### Interventions and study plan

Written informed consent will be obtained from all eligible patients before enrolment. Subsequently, all enrolled patients are screened for 10 ± 3 days (V0). During this period, their Western medication will be standardized according to their clinical conditions with reference to the 2010 HFSA comprehensive heart failure practice guideline [5] and 2007 CSC guidelines for the treatment and diagnosis of chronic heart failure [6]. The standardized Western medications include diuretics, angiotensin-converting enzyme inhibitor or angiotensin-receptor blocker, β-blockers, aldosterone receptor antagonist, digoxin, and vasodilating agents. To achieve a heart-healthy lifestyle, patients will also be advised to restrict salt and water intake, monitor weight, and maintain regular physical activities.

After screening, stable patients will be randomized to either a treatment or control group at the baseline visit (V1). Besides their standardized Western medicine, patients assigned to the treatment or control group will take QSYQ or placebo, respectively. Patients have to take one packet (0.52 g) of the study medication thrice daily, with the first dose taken as soon as practically possible. Independent drug administrators will be responsible for the delivery and dispensation of the study medications.

This trial has two phases: treatment and follow-up. In the 6-months course of treatment, study medications will be given to the patients, who are to attend study visits at 1, 3, and 6 months (V2, V3, and V4). After the treatment phase, patients will enter a follow-up phase lasting for at least another 6 months. During this follow-up period, patients are to attend study visits at 9 and 12 months (V5 and V6), and two additional study visits during extended follow-up (V7, V8). The extended follow-up ends when the last patient enrolled into the trial completes 12 months of treatment and follow-up. All the visits and contents are described in Figure 1.

**Figure 1 F1:**
[figure not shown]
Study visits.

During the entire trial period, any other kinds of TCM drugs are forbidden except for QSYQ or the placebo. The study medication should be taken routinely for 6 months unless disallowed because of certain clinical conditions. In the case of comorbidities (such as hypertension or diabetes) and complications, appropriate Western medicine can be given with reference to the relevant guidelines. All drugs used should be recorded up to date by the investigators. Patients should not hesitate to seek emergency care if necessary.

### Outcomes

#### Primary outcome

The 6MWT will be used to assess the exercise capacity of the patients in this trial [22]. This test will be used for each patient at study visits V1, V3, and V4, and conducted in hospitals on a 30-meter track. The patients will be instructed to walk as far as possible for 6 minutes, at a self-determined speed and pausing to rest as needed. Before each test, the patient’s blood pressure, heart rate, and oxygen saturation will be measured. Subsequently, effort perception on the Borg scale will also be assessed. At the end of each test, the same parameters will be measured again. The result of the 6MWT is the total distance covered (in meters) in 6 minutes.

#### Secondary outcomes

Composite endpoints, including all-cause mortality, frequency of hospitalization or emergency due to cardiovascular events (exacerbated HF, acute coronary syndrome, malignant ventricular arrhythmias, cardiac shock, revascularization, stroke, pulmonary embolism, peripheral vascular events, and so on) will be documented at study visits from V2 to V8. Additional secondary outcome measures, such as brain natriuretic peptide levels, echocardiography (including left ventricular ejection fraction quantified by the Simpson method) and cardiothoracic ratio by radiography will be included for the patients at study visits V1 and V4. The NYHA classification and Minnesota quality of life scores, as well as information from the four TCM diagnostic methods, will be documented at study visits from V1 to V6.

#### Other measurements

Blood lipid tests (blood cholesterol, triglycerides, high-density lipoprotein, and low-density lipoprotein) will be carried out at study visits V1, V3, and V4.

#### Safety

Safety will be assessed by vital signs, laboratory tests, ECG, and adverse events. Vital signs, including heart rate and blood pressure, will be monitored at enrolment and study visits V1 to V6. Laboratory tests, such as routine blood and urine tests, hepatic and renal function, and blood electrolyte levels will be examined at study visits V1, V3, and V4. Electrocardiograms will be recorded at study visits V1, V3, V4, V5, and V6. Adverse events will be documented at every study visit and severe adverse events will be reported to the principal investigator within 24 hours. In the case of a medical necessity, the patients will be unblinded according to the unblinding procedures on receiving permission from the principal investigator. A negative pregnancy test is also mandatory before enrolment of women of reproductive age.

A schedule of all evaluations is outlined in Figure 2.

**Figure 2 F2:**
[figure not shown]
Schedule of evaluations.

### Data collection

Patients will be followed up by a study investigator until the end of trial, and all general data and outcome evaluations will be recorded in the case report form at each study visit. Investigators will also update an electronic database using Oracle Clinical Remote Data Capture. This will provide real-time monitoring of the database, to ensure the high quality of data. At the end of the trial, the investigators, data managers, and statisticians will perform blind review and confirm the database before processing data.

### Ethical aspects

This trial protocol was approved by the Ethics Committee of First Teaching Hospital of Tianjin University of TCM on 2 December 2011 (TYLL2011 [K] 005). The protocol and its informed consent form have been judged ethically and scientifically satisfactory for the trial aims. Written informed consent must be obtained from all participants or their legally authorized representatives before enrollment. The trial has been registered with both the Chinese Clinical Trial Registry of International Clinical Trials Registry Platform of World Health Organization and ClinicalTrial.gov of the U.S. National Institutes of Health.

### Statistical analysis

Statistical analysis for the trial will be performed by the Centre for Statistical Science, Peking University. Statistics software SAS 9.1 will be used for the data analysis. Intention-to-treat analysis, per-protocol analysis, and safety analysis will be conducted. Calculations for the outcomes will be based on a two-tailed test, except for the primary outcome, which will be a one-tailed test (level of significance *α* = 0.05). Besides the statistical comparison between baseline variables, the change in 6MWT result between baseline and the assessment 3 and 6 months during the treatment phase will be performed using analysis of covariance adjusted for baseline and treatment to improve the efficiency and power of the tests. Survival analysis will be conducted using Kaplan-Meier and Cox regression models. Statistical analysis on the missing data of the outcome measures will be adjusted using an estimating equation or statistical model in the final analysis. Sensitivity analyses will also be performed to assess the robustness of the data.

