## Design

The CACT-IHF study is designed as a multicenter, randomized, double-blind, placebo-controlled trial, and will be conducted in 32 level-A hospitals in China. A total of 640 stable outpatients with IHF, who fulfill the inclusion and exclusion criteria, will be randomized into either a treatment group or a control group.

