### Sample size

The sample size calculation was based on results from studies by Hutcheon *et al*. [20] and Mao *et al. *[21]. After 6 months of intervention, we assume that the distance walked in a 6-minute walking test (6MWT ) in the control group and treatment group will be up to 260 m and 288 m, respectively (that is, patients in the treatment group will walk an additional 28 m, *δ* = 115 m). Patients will be randomized in the ratio of 1:1 into two groups and each group requires at least 266 patients in order to produce positive results (one-tailed test, significant level *α* = 0.05, power (1 - *β*) = 0.80). Considering the loss of patients due to follow-up and a maximum dropout rate of less than or equal to 20%, the sample size was increased to 320. To calculate sample size, we used the equation:

$$n=\frac{2{\left(Z_{1-\alpha }+Z_{1-\beta }\right)}^{2}\delta^{2}}{{\left(\mu_{T}-\mu_{C}\right)}^{2}}$$

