### Randomization procedure

Included patients will be randomly assigned to a treatment or control group in the ratio of 1:1. Stratification will be performed on NYHA classification, enrolling hospitals, and revascularization methods. Eligible patients will be randomized by IWRS/IVRS software (ClinicalSoft Co. Ltd.) into the intervention arms. The identification number and randomization code generated are unique to each patient and correspond to the coded boxes of either QSYQ or a placebo matched in appearance, color, and shape to the drug. The flavor of the drug and placebo are also similar. Blinding will be maintained amongst the investigators and patients.

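### The stated primary ANCOVA leaves out the factors used to stratify randomization; this is conservative and may forgo a little power, and it is cheap to put right

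*Protocol article*

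**What the plan says.** Randomization procedure: "Stratification will be performed on NYHA classification, enrolling hospitals, and revascularization methods". According to Design, the trial "will be conducted in 32 level-A hospitals in China", and Inclusion criteria admit NYHA classes II to IV, so there are three classes.

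Statistical analysis: the change in 6MWT from baseline to 3 and 6 months is to be compared by "analysis of covariance adjusted for baseline and treatment to improve the efficiency and power of the tests". I take 'baseline' here to mean the baseline 6MWT value. No stratification factor is named. The same section makes all tests two-sided "except for the primary outcome, which will be a one-tailed test (level of significance *α* = 0.05").

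Sample size: the calculation uses an unadjusted comparison of two means ("one-tailed test, significant level *α* = 0.05, power (1 - *β*) = 0.80"). It assumes that "patients in the treatment group will walk an additional 28 m" with a value of 115 m, which is printed as δ but serves as the standard deviation in the formula. It takes no credit for any covariate.

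**The concern.** When allocation is balanced within strata that predict the outcome, between-stratum variance is removed from the treatment contrast. A model without the strata still counts that variance as residual noise, so its standard error tends to exceed the true variability of the estimate. Where the strata are too small to be balanced, chance differences in those factors between arms remain, apart from what baseline 6MWT absorbs. In either case, adding the factors helps if they are prognostic.

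The sentence that defines the model justifies its covariate by efficiency and power. Leaving out the variables judged important enough to stratify on sits badly with that aim. At stake are the width of the interval for the primary result and a few points of power. The validity of the test is not at stake.

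**Working it through.** **Inputs from the article.** Difference 28 m; SD 115 m; one-sided α 0.05; 1:1 allocation; 266 per group before and 320 after the dropout allowance; dropout up to 20%. Evaluable per arm at full dropout: 320 × 0.8 = 256.

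**Inputs assumed, because the documents give none.** ρ, the correlation of 6-month with baseline 6MWT: 0 or 0.5. R², the share of variance left after baseline that the three stratification factors explain: 0 to 0.20.

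**The plan's own figure.** The printed formula gives n = 2(1.645 + 0.842)² × 115² / 28² = 208.6, so 209 per group. The stated 266 is not reproduced. A two-sided 5% test gives 265, which is close to it. The 320 is 266 × 1.2 = 319.2 rounded up, whereas 266 / 0.8 gives 333. These are separate matters; here they matter only because the stated one-sided test has power to spare.

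**Power with and without the factors.** Residual SD = 115 × √(1 − ρ²) × √(1 − R²); SE = SD × √(2/256); power = Φ(28/SE − 1.645).

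- ρ = 0, R² = 0: SE = 115 × 0.0884 = 10.17; 28/10.17 − 1.645 = 1.11; power 86.6%.
- ρ = 0.5, R² = 0: SD = 99.6, SE = 8.80; 28/8.80 − 1.645 = 1.54; power 93.8%.

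| Assumed R² | SE without / SE with factors, 1/√(1 − R²) | Power, ρ = 0 | Power, ρ = 0.5 |
|---|---|---|---|
| 0 (same as omitting them) | 1.000 | 86.6% | 93.8% |
| 0.02 | 1.010 | 87.2% | 94.2% |
| 0.05 | 1.026 | 88.1% | 94.7% |
| 0.10 | 1.054 | 89.6% | 95.6% |
| 0.20 | 1.118 | 92.4% | 97.2% |

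The gain is 0 to 5.8 points with ρ = 0 and 0 to 3.4 points with ρ = 0.5.

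**Check by simulation.** 512 evaluable patients, 32 hospitals, three NYHA classes, three revascularization levels (assumed), permuted blocks of 2 or 4 in every cell (assumed), ρ = 0.5, half of R² from hospital and a quarter from each other factor, 2,000 runs per setting. The adjusted model used fixed effects throughout.

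- Without the factors, the mean model SE was about 8.8 m and the actual SD of the estimate 8.1 to 8.8 m. The stated SE is therefore about right or somewhat too large.
- With the factors, the model SE was about 8.7 m (R² = 0.05), 8.4 to 8.5 m (0.10) and 8.0 m (0.20).
- Power without versus with the factors was 94.4–94.6% versus 94.4–94.6% (R² = 0.05), 92.6–94.6% versus 94.0–95.2% (0.10) and 95.2% versus 97.0–97.3% (0.20).
- Type I error was 0.040 to 0.055 without the factors and 0.048 to 0.060 with them; the simulation error is about 0.005. Neither range shows inflation beyond simulation noise.

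At R² = 0.05 the simulated gain vanishes. Fixed effects cost 31 + 2 + 2 = 35 parameters, which is a reason to treat hospital as random or to pool small hospitals.

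**If the test were two-sided.** This is not the stated plan. With ρ = 0, power at 256 per arm would be 78.7% without the factors and 80.7%, 82.7% and 84.8% with R² of 0.05, 0.10 and 0.15. With ρ = 0.5 it would be 88.9% without them.

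**The case against.** The strongest reply is that a condensed article is not a model specification. The sentence does not exclude further terms, the two sections do not contradict each other, and a statistical analysis plan that is not shown may list the stratification factors. That possibility stands. But the sentence goes beyond naming a method: it gives the adjustment terms and the reason for them, so it reads as the model. If a longer list exists elsewhere, the article describes the primary analysis incompletely and needs the same one-sentence correction.

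The reply is also right on size. Only the relation to change beyond baseline 6MWT counts, and the documents give no figure for it.

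Several stronger readings are tempting and are not supported:

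- A reader might infer that the standard error is certainly too large, that power is certainly lost, or that the p-values are wrong. With R² = 0 nothing is lost, and the test as stated is valid and at most conservative.
- A reader might infer that the trial is underpowered as a result. Under the stated one-sided test, power is 86.6% with no covariate benefit at all.
- A reader might argue that the strata are too fine to balance: 32 × 3 × 2 = 192 cells or 32 × 3 × 3 = 288 cells, hence 3.3 or 2.2 of the 640 patients per cell. The number of revascularization levels and the block size are not given, so the balance achieved cannot be judged. Poorer balance would also shrink the overstatement of the standard error, so this argument partly works against the main one.
- A reader might want the same covariates in the Cox models. That is a preference; it also changes the hazard ratio from marginal to conditional.

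**Conclusion.** The point holds in a limited form. The stated primary model does not reflect the stratified randomization. The direction of the effect is clear: conservative, with no inflation of type I error. The size is not known from the documents. It is about 0 to 6 points of one-sided power with no baseline correlation and about 0 to 3 points with a correlation of 0.5, for an assumed residual R² of 0 to 0.20 and 256 evaluable patients per arm. Confidence is high in the mismatch and its direction, and low in the magnitude. This is a free or cheap improvement of low severity.

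**What to change.** State the primary model as an ANCOVA of 6-month change in 6MWT on treatment, baseline 6MWT, NYHA class and revascularization method, with hospital as a random effect, or with small hospitals pooled by a rule fixed before unblinding. If the statistical analysis plan already does this, refer to it in the article's sentence.

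The cost is one sentence, and the factors must be known at randomization anyway. The small downside is that the handling of small hospitals (640 / 32 = 20 patients each on average) and of sparse NYHA or revascularization categories must be prespecified. Doing so before unblinding also removes any later choice between an adjusted and an unadjusted primary result. No change to the Cox models is needed for this point.

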## Discussion

The use of TCM alongside Western medicine in the treatment of HF is a common practice in China and has developed into an integrative treatment model. The efficacy of the model to improve the exercise capacity, quality of life, and symptoms of these patients has been demonstrated in some small-scale clinical studies [23-26]. However, there is a lack of high-quality evidence to support the recommendation of integrative treatment for HF.

QSYQ, as a TCM drug often used in IHF treatment, has been studied in many small-scale clinical trials and intensive experimental researches [9-19]. However, there is still a demand for a high-quality and larger-scale clinical research to prove its efficacy in the treatment of IHF. As TCM is composed of multi-active components and possesses multitarget action feature, it can provide a holistic regulation of whole body and improve overall condition of patients. To assess the results of the treatment effectively, an appropriate outcome measure is required. QSYQ has showed its advantage in increasing exercise capacity of IHF patients, therefore the 6MWT, which has been proven to be a good measurement of exercise capacity [27,28], could be a proper primary outcome test for the trial.

The study protocol was designed with reference to international clinical trial principles. Strict quality control measures were implemented and data were monitored regularly. Quality control supervisors will ensure that investigators adhere to the study protocol in each investigation center. The trial has also applied IWRS and Oracle Clinical Remote Data Capture to enhance data management and reduce bias in the research. The rigorous design of the trial will ensure an objective and scientific assessment of the efficacy and safety of QSYQ in the treatment of IHF.

## Trial status

The CACT-IHF study has been recruiting patients since March 2012. Study completion date is estimated at August 2014. Clinical trials.gov number: NCT 01555320.

## Abbreviations

6MWT: 6-minute walking test; HF: Heart failure; IHD: Ischemic heart disease; IHF: Ischemic heart failure; NYHA: New York Heart Association; QSYQ: *Qishen Yiqi* dripping pills; TCM: Traditional Chinese medicine.
